**Methods/Design:**

Adults aged ≥ 18 with a body mass index ≥ 25 and who report persistent pain (≥4 out of 0–10 for > 6 months) will be recruited for treatment at the Health Behavior Research Lab at the University of the Sciences. After baseline assessments and goal setting, participants will be randomized to receive one of three treatments. Participants will receive eleven treatment sessions delivered during 1 hour, weekly individual meetings with a clinic therapist. Follow-up will occur at 3, 6 and 12-month time points; assessments will include measures of weight and pain intensity (primary outcomes). A mixed-method approach to evaluating study outcomes will include individual interviews with participants about their treatment experience. These interviews will be led by a research staffer who was not involved in study intervention or assessment using a semi-structured discussion guide.

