**Discussion:**

This study fills an important gap in intervention research, evaluating best-practices for behavioral management of a highly prevalent co-morbidity that has sub-optimal outcomes with currently-implemented approaches. STOP’s pragmatic focus builds upon treatments already in use in clinical practice. Should STOP be found efficacious in achieving the dual outcomes of pain management and weight loss, such an approach could be integrated into practice with minimal additional cost or training.

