### Sample size and power estimation

Input data to estimate sample size needed for adequate power came from pilot data from individuals with co-morbid chronic pain and obesity enrolled in standard care, healthy lifestyle, or intensive weight loss interventions [42] and published results from a study of weight loss intervention for older obese adults with knee osteoarthritis [43]. These data informed the following assumptions: (a) SCW is associated with an 11 pound weight loss, SCP is associated with a 1 pound weight loss, and STOP is associated with a 17 pound weight loss; (b) the within-person correlation of weight over measurements is 0.96 and the between-person standard deviation is 10 pounds; (c) SCP is associated with a 2-unit reduction in pain level (on a 10-point scale), SCW is associated with no reduction in pain level, and STOP is associated with a 4-unit reduction in pain level; (d) the within-person correlation of pain over measurements is 0.89 and the between-person standard deviation is 1.6 units; and (e) the correlation between pain level and pounds lost is 0.34. Additional assumptions included 85% retention rate over 12 months, maintenance in outcomes from 3- to 12-month follow-up, and .05 Type I error rate. Power and sample size estimates were calculated with the GLIMMPSE 2.0 online tool through Sample Size Shop’s tools for multilevel and longitudinal data [44]. A sample size of 120 participants will provide power in excess of 80% to detect between-group differences and within-person change over time while allowing for study attrition.

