### Quantitative data analysis

Longitudinal outcomes will be analyzed on an intent to treat basis, including every subject who is randomized regardless of protocol adherence, study completion, or missing data. Generally, our approach will be to use mixed-effects regression models (MRMs) implemented via SAS PROC MIXED. These models do not place restrictions on the number of observations per individual; therefore, no participants will be excluded from the analysis due to missing data. In addition to using all available data, mixed models are appropriate for this study because they model individual change across repeated measures, fixed effects of baseline characteristics and treatment group, and interactions between fixed effects and continuous time [45].

For each outcome (pain intensity, weight), standard care serves as the control. For pain outcomes, STOP versus SCP and SCW versus SCP contrasts will be estimated; for weight outcomes, STOP versus SCW and SCP versus SCW contrasts will be estimated. Following the recommendations of Fitzmaurice and colleagues [46], we will model our primary outcomes at all timepoints (baseline, 3-month follow-up, 6-month follow-up, and 12-month follow-up), include both linear and quadratic effects of time and group by time interactions, control for baseline weight and baseline pain intensity, and assume the group means and variances are equal at baseline because subjects are randomized to group. Our primary tests will be for the group by time interaction terms which will indicate the extent to which treatment groups experience change in weight and pain intensity following baseline and the degree to which any observed differences are maintained over time.

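### Up to eight interaction terms are primary at a single 0.05, and no rule links them to the dual pain-and-weight claim

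*Protocol article*

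**What the plan says.** The Protocol article names two primary outcomes: in the abstract (Methods/Design), "assessments will include measures of weight and pain intensity (primary outcomes").

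Quantitative data analysis names two contrasts for each. For pain: "For pain outcomes, STOP versus SCP and SCW versus SCP contrasts will be estimated". For weight: "for weight outcomes, STOP versus SCW and SCP versus SCW contrasts will be estimated". The model covers four time points ("baseline, 3-month follow-up, 6-month follow-up, and 12-month follow-up") and is to "include both linear and quadratic effects of time and group by time interactions". The confirmatory statement is "Our primary tests will be for the group by time interaction terms".

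Sample size and power estimation lists among its assumptions "maintenance in outcomes from 3- to 12-month follow-up, and .05 Type I error rate". That is the only error rate in the article. The article does not say whether it is one- or two-sided, or how it is divided among tests.

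The Primary aim section states the hypothesis only as STOP against standard care, on weight loss, pain reduction and maintenance. The abstract's discussion puts the conclusion as a joint one, "Should STOP be found efficacious in achieving the dual outcomes of pain management and weight loss", and the main Discussion repeats the idea.

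**The concern.** The article fixes its primary tests, and the set it fixes does not match its question in two ways.

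- **The family is wider than the hypothesis.** SCW against SCP on pain, and SCP against SCW on weight, do not involve STOP. Their interaction terms still fall under the sentence that defines the primary tests.
- **The tests are listed singly, but the claim is joint.** The intended conclusion is a benefit on both pain and weight. No rule says which combination of significant terms supports it.

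Without such a rule, the 0.05 used for sizing is not the error rate of the primary analysis. A result on one term of one outcome could be reported as a significant primary finding while the dual question stays unanswered.

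**Working it through.** **1. The article's own figure.** It states power above 80% with 120 participants. Its inputs (Sample size and power estimation) are:

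- weight losses of 17 lb (STOP) and 11 lb (SCW), a difference of 6 lb; SD 10 lb; within-person correlation 0.96
- pain reductions of 4 (STOP) and 2 (SCP) units, a difference of 2; SD 1.6; within-person correlation 0.89
- 85% retention. With equal allocation (assumed), 40 per arm × 0.85 = 34.

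Using change scores, SD(change) = SD × √(2(1 − ρ)) and z = difference / (SD(change) × √(2/34)):

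- Weight: 10 × √0.08 = 2.83; 6 / (2.83 × 0.2425) = 8.7
- Pain: 1.6 × √0.22 = 0.750; 2 / (0.750 × 0.2425) = 11.0

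Both give power above 99.9%, so the stated lower bound holds. A generalised least squares calculation for the separate interaction terms (compound symmetry, full effect from 3 months and maintained) gives z = 8.85 (linear) and 7.05 (quadratic) for weight, and 11.39 and 9.01 for pain.

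**2. Number of primary tests.** 2 outcomes × 2 contrasts × 2 time terms = 8. Of these, 2 × 1 × 2 = 4 involve STOP.

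**3. Error rate under a global null.** If the tests were independent, it would be 1 − 0.95⁸ = 33.7%. They are not independent, so the eight z statistics were simulated as multivariate normal with |z| > 1.96 counted as significant. The correlations were:

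- *Between contrasts that share one arm:* 0.5 in size, which follows from equal arm sizes.
- *Between outcomes:* 0.34. This is the article's correlation of pain level with pounds lost, used here as the correlation between test statistics. With 0 instead, 20.9% becomes 21.3%.
- *Between linear and quadratic terms:* −0.96 for uncentred months at 0, 3, 6 and 12 under compound symmetry. It is about −0.47 for centred time and 0 for orthogonal polynomials. The article states no coding.

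| How the primary tests are read | Chance of at least one false positive |
|---|---|
| 8 separate terms, uncentred months, compound symmetry | 21% |
| 8 separate terms, uncentred months, AR(1) | 22–23% |
| 8 separate terms, centred time | 29–30% |
| 8 separate terms, orthogonal polynomials | 30–32% |
| One 2-df test per contrast (4 tests) | 17% |
| One 4-df test per outcome (2 tests) | about 10% |
| 4 STOP terms only, uncentred months | 12% |
| 4 STOP terms only, centred or orthogonal | 17–19% |

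**4. If both outcomes were required.** With any STOP term counting within an outcome, the global-null figure is about 0.4–1%. The relevant worst case is different: one outcome truly benefits and the other does not. The error is then the chance of any significant STOP term on the null outcome. From the STOP-only figures at zero cross-outcome correlation, this is 1 − √(1 − 0.122) = 6.3% in uncentred months and 1 − √(1 − 0.186) = 9.8% with orthogonal coding. Requiring both outcomes holds 5% only if each has a single test.

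**The case against.** - **Scope.** This is a journal article, and multiplicity rules are often left to a full protocol or analysis plan that is not shown. That stands for a missing adjustment method. It does not cover the sentence that makes plural interaction terms primary, including terms that do not concern STOP. A later plan would have to narrow that definition.
- **The 21% is not the article's figure.** This stands. Of the correlations used, only 0.34 is in the article. Time coding, covariance structure and separate testing of terms are assumptions, so the size has to be given as a range.
- **A reader might infer that any one significant term makes the trial positive.** The article does not say so. Its hypothesis and both discussions point towards needing both outcomes. The defect is that this intention is not a rule, not that the opposite rule was adopted.
- **A reader might infer that a chance SCW–SCP difference could be read as success for STOP.** Nothing in the article supports that. The planning assumptions have these arms differing by 11 − 1 = 10 lb and 2 − 0 = 2 pain units, so a significant difference there could well be true. The article also says only that these contrasts will be estimated. The global null is a reference point and not the scenario the investigators expect.
- **A reader might infer that requiring both outcomes cuts power to 67%.** That is the joint power of two tests at 80% each with correlation 0.34. It does not describe this trial, whose inputs give above 99.9% for each test.

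**Conclusion.** The concern holds as a badly fixed primary analysis. Up to eight interaction terms are primary, half of them outside the STOP hypothesis, with one 0.05 and no rule linking them to the dual-outcome claim.

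The error rate cannot be given as one number. Under a global null at two-sided 0.05 per test, it runs from about 10% (one test per outcome) to about 32% (eight separate terms, orthogonal coding). The 21% figure belongs to eight separate terms in uncentred months. Even the lowest figure is about twice nominal. Only a reading that requires both outcomes falls below 5% under the global null, and the article does not state that reading as a rule.

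The trial remains interpretable. The criterion for success should be fixed before outcome data are seen.

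**What to change.** Keep the mixed model in Quantitative data analysis, and state the following.

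1. **One confirmatory contrast per outcome:** STOP against SCW for weight, and STOP against SCP for pain. Test each once, either as the model-based difference at 6 months or as a single 2-df group-by-time test. The 2-df test is not directional, so if it is chosen, also require the estimated difference to favour STOP.
2. **Success rule:** claim the dual benefit only if both tests are significant at two-sided 0.05. A false dual claim then needs rejection of at least one true null at 0.05, so no alpha split is needed.
3. **Maintenance:** if both succeed, test the 12-month contrasts in a fixed order, as tests of the primary aim.
4. **Other contrasts:** label SCW against SCP, on both outcomes, as secondary.
5. **Time coding and joint power:** state both.

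**Cost.** No extra participants are needed, but this is more than a change of wording, because it sets which quantity is confirmatory. Joint power is below single-outcome power. On the article's inputs, with 34 per arm and equal allocation assumed, each contrast exceeds 99.9%, so joint power is at least 1 − 2 × 0.001 = 99.8%.

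**Alternative.** To keep all eight terms primary, a Bonferroni level of 0.05 / 8 = 0.00625 holds the familywise error at or below 5%. Power for each STOP term stays above 99.9% on the same inputs. It would still need a rule for the dual claim.

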### Qualitative data collection

Following the completion of treatment, all participants will be asked about their willingness to participate in a one-on-one interview about their treatment experience. To reduce bias, purposeful sampling will be employed by inviting a sample of representative participants from all three intervention groups including participants who completed and dropped out of treatment. This sampling strategy will insure that participants vary with respect to age, gender, treatment outcome, and study completion [47].

Willing participants will be interviewed by a trained member of the research staff who was not involved in leading the intervention or study assessments. Interviews are expected to last between 30 and 60 minutes. Interviewers will use a semi-structured discussion guide and follow a funnel structure progressing from broader, open-ended questions to more specific probes to clarify issues as needed. This approach will allow for flexible, thorough, and detailed data collection.

The interview protocol begins with questions designed to build rapport with participants (see Table 3 for interview protocol). Next, a series of questions elicit participants’ feedback regarding their direct experiences with the program. During the course of the interview, questions may be re-worded, re-ordered, and/or clarified to further investigate topics as introduced by the respondent. All interviews will be audio recorded and transcribed verbatim. Study participants will be invited for an interview until theoretical saturation is reached, which is the point in analysis and data gathering where all categories are well developed in terms of properties, dimensions, and variation and no new themes have been identified [48].

**Table 3 T3:** Qualitative interview questions

**Type**	**Question**
Rapport, priorities, preference	1. Why were you interested in participating in this study?
	2. Why did you decide to participate after you learned about the study details?
	3. What were your thoughts when you found out you were randomized to [pain, weight loss, integrated intervention]?
	4. How did your view of the intervention change as you progressed through the study?
Experience	5. Describe for me the most important or useful ways to manage [weight loss, pain, both] that you learned from your sessions?
	6. What were some things covered in the sessions that were not useful for you?
	7. What do you do differently now based on what you’ve learned during treatment?
	8. How did you feel about the weekly homework assignments?
	9. How will you continue to use the skills you learned?
Experience, reflection, priorities	10. Why do you think you had the outcome you did in treatment [lose weight, experience less pain, both, neither]?
	11. What is the most important thing healthcare providers need to know about treating someone with comorbid pain and overweight?
	12. What do you think are the most important outcomes for treatment? For you, what would define a ‘good outcome’ to a treatment such as this?

### Qualitative data analysis

Once transcribed, interview text will then be verified for content accuracy by the lead investigator and two research assistants. The constant comparative method [49] will be used to analyze the data. Using this iterative approach, a pair of research assistants who did not participate in data collection, along with study staff who conducted interviews, will independently read the transcripts. They will then develop an initial list of themes from this data. Transcripts will be coded with relevant text identified for each code. Themes will be revised and refined through a second reading of study transcripts and subthemes will be created [50].

## Discussion

The proposed research is significant in that it will evaluate best-practices for behavioral management of a highly prevalent co-morbidity that has sub-optimal outcomes with currently-available treatments. The strength of this approach is its pragmatic focus. The study intervention builds upon treatments that already have demonstrated efficacy to improve pain and weight outcomes separately and are already in use in clinical practice. The current study examines these standard care behavioral approaches and compares them to an integrated approach that utilizes these evidence-based tactics in a novel way. Therefore, should an integrated treatment be found efficacious in achieving the dual outcomes of pain management and weight loss, such an approach could be integrated into clinical practice with minimal additional cost or training.

While the study will examine alternatives for treatment of pain and obesity in a setting with relevance to ‘real world’ practice, an additional advantage of this study is that the patient population will also more closely mirror those seen in clinical practice. Therefore, findings should be readily generalizable. Currently-available evidence examining treatment approaches for co-morbid chronic pain and obesity includes randomized clinical trials with very specific inclusion/exclusion criteria [16,26]. The planned intervention evaluates a treatment approach adoptable for a wider variety of pain conditions and for patients that have a number of other concurrent health issues that likely would render them excluded from most clinical trials. Thus, the patient population in STOP will closely mirror individuals who are likely to be seen in practice care settings. Findings generated from this study will have particular relevance in understanding how evidence-based approaches may perform with such populations in everyday clinical environments.

Finally, this study is innovative in that it is applying a mixed-methods approach to identify processes of change, treatment approaches, and clinical outcomes most relevant to patients. We aim to obtain potential explanations for any observed treatment effect using not only quantitative measures (e.g., Therapy Evaluation Form, Stages of Change) but also individual interviews. Qualitative research techniques such as those included here offer a comprehensive yet flexible approach particularly suited to understanding the individual’s subjective experience. Information gathered via participant interviews will offer complimentary, detailed information to aid in our understanding of treatment-promoted change in weight and/or pain outcomes. Examining how individuals with obesity and chronic pain understand and experience treatment is important to implementing more effective interventions. Indeed, such insights may provide a foundation to improve treatment implementation which will further aid in developing testable hypotheses about mechanisms of effect.

As with any intervention trial, this study has several limitations. Most significantly, while pragmatically-focused studies such as this one offer high external validity, this likely comes at a cost to internal validity. It may be difficult to identify which specific components of treatment are most actively beneficial. Additionally, while all three arms are explicitly specific in their focus (pain, weight, integrated), there is a certain degree of overlap in treatment topics across all three interventions. While we have made every attempt to adequately power the trial, it is not clear whether this overlap is significant enough to render treatment effects across the three interventions clinically and/or statistically non-significant.

In sum, the STOP study represents an important next step in understanding how to treat a common and costly co-morbidity. The trial will answer the questions of how to provide optimal care to simultaneously achieve improved pain management and weight loss. Of significant importance is the potential for the findings from this trial to be quickly implemented in existing care structures to better meet the needs of individuals with both obesity and chronic pain.

## Abbreviations

STOP: Simultaneously Treating Obesity and Pain; SCW: Standard Care Weight; SCP: Standard Care Pain; BMI: Body Mass Index; IRB: Institutional Review Board.
